# A randomized controlled trial protocol comparing low-calorie Mediterranean and low-carbohydrate diets for diabetes remission in individuals with type 2 diabetes in northern Lebanon: an intervention mapping–based approach

**DOI:** 10.3389/fpubh.2026.1787980

**Published:** 2026-04-08

**Keywords:** behavior change, diabetes remission, intervention mapping protocol, lifestyle modification, Mediterranean diet, mobile health application, type 2 diabetes mellitus, weight loss

## Abstract

**Background:**

Type 2 diabetes mellitus (T2DM) is increasing worldwide, largely due to obesity and unhealthy lifestyle behaviors. Weight-loss–induced diabetes remission offers a promising approach to reducing complications and improving quality of life. Addressing this effectively requires a comprehensive approach that targets behavioral and environmental determinants and is guided by the Intervention Mapping (IM) protocol.

**Objective:**

This paper describes the protocol for a randomized controlled trial comparing two low-calorie dietary approaches for achieving diabetes remission in adults with T2DM, using an IM-based intervention framework.

**Methods:**

This is a two-phase, multi-center, parallel-group randomized controlled trial conducted in primary medical centers in Northern Lebanon. A total of 50 adults aged 18–65 years, with a maximum diabetes duration of 6 years and treated with oral antidiabetic medications, are enrolled. Participants are randomly assigned to follow either a low-calorie Mediterranean-style diet or a low-calorie, low-carbohydrate diet. The study consists of a 6-month weight loss phase developed using the six steps of the (IM) protocol, followed by a 6-month maintenance phase supported by a mobile health application, resulting in a total follow-up duration of 12 months. The primary outcome is diabetes remission at 6 months (HbA_1c_ < 6.5% with or without discontinuation of medication). Secondary outcomes include sustained remission at 12 months, changes in weight and body composition, glycemic control, lipid profile, sleep quality, physical activity, psychological stress, and inflammatory markers. Secondary outcomes will be assessed at baseline and every 3 months and analyzed exploratorily.

**Discussion:**

Sustained weight loss is essential for achieving diabetes remission and reducing metabolic complications; however, long-term success depends on realistic and maintainable behavioral changes. This protocol applies the IM framework to systematically develop a culturally relevant, theory-based intervention tailored to individuals with T2DM in Lebanon. By combining dietary strategies with behavioral support and mobile health technology, the study addresses barriers to long-term adherence. The findings are expected to inform the design of scalable, context-specific interventions for diabetes management in similar low- and middle-income settings.

**Clinical trial registration:**

https://www.isrctn.com/ISRCTN99204002, Identifier ISRCTN99204002.

## Introduction

Diabetes represents one of the most rapidly escalating global health challenges, significantly impacting individuals, families, and communities. As a serious, long-term condition, it is among the ten leading causes of adult mortality, claiming approximately 6.7 million deaths worldwide in 2021 (1) and affecting 9.3% of the global population in 2019 (2) and 10.5% in 2022 (3), a figure expected to rise to 10.9% by 2045 (2). The Middle East and North Africa regions have the highest prevalence, with rates projected to reach 13.9% by 2045 (2, 4). In Lebanon, 7.8% of adults aged 20–79 live with Type 2 Diabetes Mellitus (T2DM) (5) which accounts for approximately 90 to 95% of all diabetes cases (6). T2DM contributes to premature mortality, increased healthcare costs, and reduced quality of life (2, 7, 8). In addition to its clinical burden, T2DM imposes substantial financial costs estimated at 760 billion dollars globally in 2019 (2) and affects productivity through increased absenteeism (8, 9). According to the American Diabetes Association (ADA), healthcare spending per person with diabetes is 2.3 times higher than for those without the disease, with a substantial portion of costs linked to diabetes-related comorbidities (10). In the Middle East, the mean hospitalization cost for individuals with diabetes reached approximately $1,436, surpassing the International Diabetes Federation’s global per-person cost estimate (11).

Obesity is the leading cause of T2DM and a key contributor to its growing prevalence (12). This condition has become increasingly prevalent across the globe, raising significant concerns that the World Health Organization has termed this issue an “escalating global epidemic” (3). It is one of the most visible health problems impacting people of all ages and socioeconomic backgrounds worldwide (13). In 2022, approximately 2.5 billion adults were classified as overweight, with 890 million living with obesity. Projections suggest that by 2050, this number could rise to 3.8 billion adults experiencing overweight and obesity (13). The growing burden of these conditions is closely linked to a higher incidence of T2DM and various cardiometabolic complications. This is primarily due to abdominal fat, which can lead to insulin resistance, pancreatic dysfunction, and increased inflammation, ultimately contributing to greater morbidity and mortality rates (14, 15).

For years, medical treatments and lifestyle modifications have been the cornerstone of diabetes control, promoting weight loss, physical activity (PA), and a healthy diet (16–18).

Since obesity is a significant risk factor for T2DM and its associated complications, weight loss is strongly recommended to enhance insulin sensitivity and delay the need for exogenous insulin 19. Evidence shows that 10–15% weight loss, achieved through bariatric surgery or intensive dietary interventions, can induce diabetes remission (18–22).

Dietary modification, therefore, represents a practical and sustainable approach to achieve such weight reduction and metabolic improvement. Among nutritional approaches, the Low Carbohydrate (LC) diet and the Mediterranean Diet (MD) have shown promising improvements in metabolic profiles, often linked to weight loss (23–26), and have been investigated for T2DM management and remission (27, 28). LC diets have a carbohydrate content of less than 45% and are further categorized into three groups: very LC or ketogenic LC, which contains less than 10% of carbohydrates, LC diet, which has a range of 10 to 26% of carbs or less than 130 g of carbohydrates per day, and moderately LC, which includes 26 to 45% of carbohydrates (27, 29, 30). A systematic review examining the dose-effect of carbohydrate restriction found that moderate carbohydrate restriction (26–45%) resulted in reductions in blood glucose levels, HbA1c, and blood lipids over six months when compared to high-carbohydrate diets (31). However, these effects became insignificant after six months, particularly with very low-carbohydrate diets, likely due to low adherence (31). On the other hand, research indicates that a range of dietary patterns, including traditional MD, appears suitable for translating nutritional recommendations into practical advice for individuals with diabetes (32, 33), a finding previously validated in a systematic review comparing several dietary approaches for the management of T2DM (34). In a 16-week weight-loss study, patients with T2DM who followed an LC or an MD diet experienced significant reductions in blood sugar, fat levels, and glycated hemoglobin (HbA1c), with the LC diet showing slightly better results because it led to greater weight loss than the MD diet (35). However, the restrictive nature of the LC diet, which contains less than 130 g of carbs, led to cravings and difficulty maintaining dietary variety, factors that make the MD easier for people to adhere to over time and a better option for managing T2DM in the long run (34, 35).

In 2021, the ADA defined diabetes remission as maintaining an HbA1c < 6.5% for at least three months without glucose-lowering medication (36, 37). However, achieving remission is often hindered by adherence challenges (38) such as poor health literacy, obesogenic environment, poor self-esteem, ambivalence, and socioeconomic factors, particularly in low-resource settings like Lebanon, where socioeconomic status and limited health awareness are common barriers (39).

In this trial, the number of participants achieving remission (HbA1c < 6.5%) without medication will be reported separately from those who achieve HbA1c < 6.5% while continuing pharmacotherapy. This approach was adopted to account for potential reluctance among physicians to discontinue cardiometabolic medications in routine clinical practice. Concerns about rebound hyperglycemia, patient destabilization, and the risk of adverse outcomes may limit medication withdrawal (40). Furthermore, delays in deprescribing may also stem from the absence of well-established guidelines, which can contribute to cautious prescribing behavior, particularly in settings characterized by high levels of daily stress and healthcare system instability (41).

Managing diabetes complications and achieving remission, hence, requires a multidisciplinary team (42). Physicians play a crucial role in communicating the potential for diabetes control, specifically the ability to achieve glycemic stability, delay disease progression, and, in some cases, induce remission through dietary and lifestyle modifications (43). By framing these possibilities in a patient-centered manner and facilitating referrals to dietitians for sustained support, they help initiate and sustain behavior change. Given the personal and environmental barriers to T2DM management (44–46), tailored interventions are essential. The Intervention Mapping (IM) framework provides a flexible and systematic structure for developing such interventions, ensuring that programs are both theory-driven and evidence-based while being adapted to the Lebanese context (47).

The present study aims to systematically document the development process for designing a two-arm dietary intervention using the IM protocol. The trial is designed to compare the effects of a calorie-restricted MD diet and a calorie-restricted LC diet on remission of diabetes. In addition to the remission outcome, the trial examines changes in cardiometabolic risk factors during the 12-month follow-up period.

## Methodology

This manuscript presents the protocol of a randomized clinical trial and adheres to the SPIRIT 2013 statement, which promotes transparency and methodological rigor in the reporting of clinical trial protocols (48). While SPIRIT provides the framework for describing the trial design and procedures, the intervention tested in this study was developed using the IM approach. The key SPIRIT components are outlined below, followed by a description of the intervention development process based on the IM framework.

### Study design

This is a two-phase, multicenter, parallel-group randomized controlled trial conducted in primary medical centers in Northern Lebanon. In the first phase, participants are randomly assigned to a low-calorie MD-style diet or a low-calorie LC diet (<130 g/day) and followed for 6 months, which is the weight-loss phase. Following this phase, a 6-month maintenance phase is supported by a mobile health application. The study protocol was approved by the Lebanese International University Institutional Review Board (LIUIRB-230817-JA-295) and registered in the ISRCTN registry (ISRCTN99204002). It was developed and reported in accordance with the Standard Protocol Items: Recommendations for Interventional Trials (SPIRIT) 2025 checklist, as outlined in Appendix S4.

### Eligibility

Eligible participants are adults aged 18–65 years with a diagnosis of T2DM, a body mass index ≥25 kg/m^2^, treated exclusively with oral antidiabetic medications, and with a disease duration of six years or less.

Participants are excluded if they are treated with insulin therapy, have a history of bariatric surgery, are pregnant or breastfeeding, have chronic liver or kidney disease, have an active malignancy, or have severe psychiatric disorders.

### Sample size calculation

Sample size estimation was based on the primary outcome of diabetes remission at 6 months, defined as HbA1c < 6.5% with or without discontinuation of glucose-lowering medication, a definition used in a large meta-analysis (27). The same meta-analysis reported that LC diets (<130 g/day) were associated with a remission rate of approximately 57% at 6 months.

For the MD group, a remission rate of approximately 15% at 12 months was reported in medication-naïve individuals (49). Given that remission rates are known to be lower among individuals receiving glucose-lowering therapy, as demonstrated in large observational cohorts (50, 51), this supports a conservative estimate for the present study population, which includes participants treated initially with oral antidiabetic medications. Furthermore, as no large randomized trials have reported diabetes remission at 6 months following an MD, and considering evidence from long-term intervention studies showing a decline in remission rates over time, including the DiRECT (52) and Look AHEAD (53) trials, a conservative remission rate of 15% at 6 months was assumed for the MD in the present trial.

It should be acknowledged that the remission estimates used for the sample size calculation were derived from studies conducted in different medication contexts. In both cases, remission was based on the same glycemic threshold (HbA1c < 6.5%). However, the estimate for the MD was derived from a study conducted in medication-naïve individuals, whereas the remission estimate for the LC diet was obtained from studies in which participants were receiving glucose-lowering therapy and remission was defined irrespective of medication use. Therefore, the two estimates are not fully comparable. Nevertheless, in the present trial, remission is defined consistently for both intervention arms as HbA1c < 6.5% regardless of medication use. In the absence of randomized trials reporting remission following an MD in medicated populations, the 15% rate was retained as a conservative estimate for the power calculation.

Using these expected remission rates (57% vs. 15%) and a two-sided *α* level of 0.05 with 80% power, the required sample size was estimated at 38 participants. To account for an anticipated attrition rate of approximately 20%, a total sample size of 50 participants was targeted.

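### The 15% Mediterranean-arm rate is called conservative for power, but against a fixed 57% a low rate favours power; the stated 80% is conditional on a 42-point difference

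*Protocol article*

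**What the plan says.** All of this is in the protocol article, section Sample size calculation. The primary outcome is remission at 6 months, and "remission is defined consistently for both intervention arms as HbA1c < 6.5% regardless of medication use". For the LC arm, a meta-analysis is cited in which such diets "were associated with a remission rate of approximately 57% at 6 months". For the MD arm, "a remission rate of approximately 15% at 12 months was reported in medication-naïve individuals".

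Two reasons are given for carrying 15% over to 6 months in a drug-treated population. One is that "remission rates are known to be lower among individuals receiving glucose-lowering therapy". The other is introduced by "considering evidence from long-term intervention studies showing a decline in remission rates over time". From these the article concludes that "a conservative remission rate of 15% at 6 months was assumed for the MD in the present trial".

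It then concedes that the two rates come from different medication contexts and cannot be fully compared, but ends by saying that "the 15% rate was retained as a conservative estimate for the power calculation". With 57% against 15%, two-sided alpha 0.05 and 80% power, it arrives at 38 participants, raised to 50 for about 20% attrition. No other MD rate is examined.

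**The concern.** Whether an assumed rate is conservative depends on what it is used for. As a forecast of how well the MD arm will do, 15% may be cautious. For power, what counts is the difference between arms. With LC held at 57%, lowering the MD rate enlarges that difference and cuts the sample size. The article applies the word explicitly to the power calculation, where it has the wrong sign.

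The supporting argument from decline over time also runs backwards. If remission fades, a 12-month figure of 15% implies a 6-month figure above 15%, not one equal to it or cautiously below it.

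This is the trial's only power statement, and it is given for a single MD rate. A reader told that the input is conservative will take 80% as a floor. If the MD rate at 6 months is above 15%, 80% overstates the power, and the loss is steep at this sample size.

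**Working it through.** **Inputs (Sample size calculation).** LC 57%; MD 15%; two-sided alpha 0.05; power 80%; 38 evaluable; 50 enrolled; attrition about 20%. The allocation ratio is not stated; 1:1 is assumed, so 19 evaluable per arm, or 25 per arm if nobody is lost.

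**Step 1: reproduce the plan's figure.** Arcsine formula, n per arm = 2(1.960 + 0.842)² / h², with h = 2·asin(√0.57) − 2·asin(√0.15) = 1.711 − 0.795 = 0.916. This gives n = 2 × 7.849 / 0.839 = 18.7, so 19 per arm and 38 in total, as stated. The pooled-variance normal formula gives 19.3, so 20 per arm and 40 in total. For attrition, 38/0.8 = 47.5 and 40/0.8 = 50. The arithmetic is sound.

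**Step 2: direction of each argument about the MD rate.**

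| Argument in the article | Implied MD rate relative to 15% | Effect on true power |
|---|---|---|
| Remission declines over time; source is at 12 months, endpoint at 6 | above | lower |
| Endpoint counts HbA1c < 6.5% on continued drugs; source participants were medication-naïve | plausibly above | lower |
| Remission is lower in drug-treated people | below | higher |

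The first follows directly from the article's own statement. The second is plausible, but no figure supports it. The third is the only one under which 15% would be conservative for power.

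**Step 3: power over a range of MD rates.** The documents give no MD rate under the trial's own definition, so the range is an assumption. LC is held at 57%. Power is the sum of the products of the two binomial probabilities over all outcome pairs for which the uncorrected Pearson chi-square test has p < 0.05. That test is the score test of the unadjusted logistic model, which is the kind of model the article plans.

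| MD rate | Difference (points) | Power, 19 per arm | Power, 25 per arm |
|---|---|---|---|
| 10% | 47 | 91.5% | 96.9% |
| 15% | 42 | 82.1% | 90.9% |
| 20% | 37 | 69.5% | 81.1% |
| 25% | 32 | 55.0% | 68.1% |
| 30% | 27 | 40.8% | 53.5% |
| 35% | 22 | 28.3% | 39.0% |

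The normal approximation at 19 per arm gives 79.4% at MD 15%, 66.1% at 20%, 51.9% at 25% and 38.5% at 30%, within about 4 points of the exact values.

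**Step 4: sample size sensitivity.** For 80% power by the pooled formula, the evaluable total is 30 at MD 10%, 40 at 15%, 52 at 20%, 72 at 25% and 104 at 30%. The required number falls as the assumed MD rate falls, which is the opposite of a conservative choice.

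**The case against.** The strongest defence is that the article gives an explicit reason to expect less than 15%: lower remission in people on glucose-lowering drugs, which describes everyone enrolled. On that reason alone 15% is conservative for power, and at MD 10% the 19-per-arm power is about 91.5%. This stands as far as it goes. It may be weak if the cited cohorts counted only drug-free remission, but their definition is not given, so it cannot be dismissed. It does mean a reader should not infer that all of the article's arguments point to a higher MD rate, or that 80% has been shown to be optimistic.

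The mismatch between the two source rates is also disclosed, with the explanation that no randomized trial supplies an MD rate in medicated patients. That is fair, and the mismatch is not hidden. The disclosure does not correct the word used for the power calculation in the sentence that closes it.

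Three stronger readings are tempting and not supported:

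- The Introduction describes a 16-week comparison of the two diets "with the LC diet showing slightly better results because it led to greater weight loss than the MD diet". It concerns glucose, fat levels and HbA1c, not remission below a threshold, so it cannot set or refute a 42-point remission difference.
- A reader might infer that a non-significant result is likely. That needs power below 50%, which at 19 per arm requires an MD rate somewhere between 25% and 30%, and at 25 per arm between 30% and 35%. Nothing in the document establishes such a rate.
- A reader might infer that a null result will be taken as equality of the diets. No passage plans this, and Statistical methods already commits to odds ratios with 95% confidence intervals.

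**Conclusion.** The concern holds in a limited form. The description of 15% as conservative for power is wrong as written, and the decline-over-time argument is misapplied. The calculation itself is correct for 57% against 15%. What is not established is the MD rate at 6 months under the trial's definition: the article's own arguments pull in both directions, so the 80% is conditional, not demonstrably too high.

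The dependence is large. Each 5-point rise in the MD rate from 15% to 35% costs about 12 to 15 points of power at 19 per arm. The enrolment target gives some cushion: with all 50 analysed, power at MD 20% is still 81.1%. These figures assume 1:1 allocation, LC fixed at 57% and an unadjusted two-group test.

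**What to change.** In Sample size calculation:

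1. Delete the word conservative wherever it describes the MD rate.
2. Stop citing decline over time in support of a low 6-month rate; if it is mentioned, say that it points above 15%.
3. State that 80% power applies only to a difference of about 42 points (57% against 15%).
4. Replace the single figure with power over a range of MD rates, for example 10% to 35%, at 19 and 25 per arm, as in the second table above.

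The cost is some rewording and one small table. No extra enrolment is needed, and neither the endpoint nor the analysis changes. The downside for the investigators is a less favourable stated power.

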### Randomization

Randomization (by minimization) was performed in the two arms using the computer-generated program “QMinim,” which ensures balance across pre-specified covariates, including age, sex, diabetes duration, and baseline BMI. The allocation sequence was generated by a research assistant who is not involved in enrolling participants or delivering the interventions.

### Intervention

Participants are randomly allocated to one of two dietary intervention arms: a low-calorie MD or a low-calorie LC diet. The intervention is delivered in two sequential phases: an initial weight-loss induction phase followed by a maintenance phase.

#### Phase 1: weight-loss induction (0–6 months)

During Phase 1, participants are randomly divided into two groups. One group follows an LC diet, consuming less than 130 grams of carbohydrates per day, while the other group follows an MD. Both groups receive personalized dietary counseling based on the six steps of the IM framework. The intervention aims to promote weight loss (10–15% of body weight) and enhance diabetes self-management through structured nutrition education, goal setting, behavioral strategies, and regular follow-ups with trained dietitians to achieve remission of diabetes.

Both groups receive comparable frequency and intensity of counseling sessions to ensure standardized behavioral support, differing only in dietary composition. Educational materials and personalized meal plans are provided in accordance with the assigned diet.

